#### Active Control Group: ST

The control condition will be a structurally similar web-based session of supportive therapy. The goals of supportive therapy are to encourage the client to identify and express feelings and to share their emotions—both positive and negative—with close others. The ST group does not teach or emphasize specific skills or beliefs. The active control group includes the same number of activities as the SIGMA and SSI-GP interventions. Also, to mirror the intervention groups as closely as possible, supportive therapy will include vignettes written by similar school-aged youths, who describe times when they benefited from sharing their feelings with friends or family members.

### Implementation Strategies

As the SSIs in this study are all self-administer web-based interventions, we adopt 5 strategies to ensure the interventions are understandable, relevant, acceptable, engaging, and effective. These strategies will also help promote context sensitivity among school students in the Chinese context.

First, we form a youth advisory group to make sure the intervention content is understandable and relevant to students’ life. The group includes 2 secondary school students of the targeted age group, 2 school social workers, and 2 university students. For example, the testimonials of anxiety situations and coping should be context-adaptive, and the introduction of scientific knowledge should be in plain language and easy to understand. The youth advisory group includes students from the target population, school social workers and counselors, and local university students. We seek their feedback and suggestions during the development and the pilot test of the study to further improve the intervention.

Second, we adopt the philosophy of solution-focused brief therapy. We do not focus on the problem but seek future-oriented solutions relevant to daily living. These techniques can help engage the participants to make the intervention relevant and can ensure the intervention is solution-focused rather than problem-focused.

Third, we integrate “design art and computing science” to make the intervention engaging; for example, we design animation icons and design videos, and use clickers in the self-administrative intervention to maintain the focus of the participants.

Fourth, we empower student participants to act as “helpers” or “experts” by framing the participants as active contributors in the improvement of the intervention and by asking them to provide support to peers [10,11]. This design aligns with adolescents’ desire for respect [22].

Fifth, to ensure the intervention will be conducted in a standardized surrounding, the intervention will be conducted in activity rooms in each school. Around 12 to 20 student participants with parental consent will be invited to participate in the intervention as a group under the support and administration of well-trained research assistants. We also monitor the time spent on each part of the presentation with computing programming techniques. Participants with too long and too short duration time (usually above 2 SDs) in 1 section will be double-checked on their participation effectiveness, and biased data will be eliminated.

### Data Collection and Management

Assessments will be conducted by a blinded researcher trained in using the instruments. Self-rated scales will be completed by the participants under guidance. All the measures have been pilot-tested, and the questionnaires take about 20 minutes to be completed. Two attention-checking items will be included in the surveys of each time point for careless responding screening (eg, “Please choose *Strongly Agree* for this item”). Only those who answer both attention-checking items correctly each time will be included in the final data analysis [23]. As the literature has shown motivation playing pivotal roles in people’s behavioral change, we will also add 2 items at the beginning of the survey at baseline to assess participation motivation of our participants with a 6-point Likert scale, asking about their motivation to participate in this program and improve their emotion regulation ability, respectively.

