**Methods:**

Adolescents (N=549, ages 12-16 years) from secondary schools will be randomized to 1 of 3 intervention conditions: the SIGMA, SSI-GP, or active control. The implementation of each intervention is approximately 45 minutes in length. Adolescent participants will report anxiety symptoms (primary outcome), perceived control, hopelessness, attitude toward help-seeking, and psychological well-being at preintervention, the 2-week follow-up, and the 8-week follow-up. A pilot test has confirmed the feasibility and acceptability of SIGMA among adolescents. We hypothesized that SIGMA and SSI-GP will result in a larger reduction in anxiety symptoms than the control intervention during the posttest and 8-week follow-up period. We also predict that SIGMA will have a more significant effect than SSI-GP. We will use the intention-to-treat principle and linear regression-based maximum likelihood multilevel models for data analysis.

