### Participant Eligibility and Randomized Control Process

Eligible participants (aged 12-16 years) in grades 7-9 will be recruited from 6 secondary schools through cluster randomized sampling. The inclusion criteria will include (1) ages between 12 and 16 years, (2) Chinese youth who can read and write Chinese, (3) enough visual and auditory abilities to complete the intervention and assessment, and (4) ability to give assent to participate in the study.

Exclusion criteria will include (1) no parental consent; (2) inability to stay focused to complete the intervention, which is approximately 45 minutes; and (3) intellectual disability or severe illness or pain that would lead to significant bias in students’ health and mental health situation. Eligible participants will not be screened for their anxiety symptoms; thus, this study will comprehensively examine the efficacy of the interventions for students with mild, moderate, and severe levels of anxiety.

The school and student recruitment process will include the following steps. First, we will send research invitations to schools chosen randomly from the school list. Invitations will stop when 6 schools agree to participate. At least 3 classes in the same selected grade of each school will be randomly selected to join the study, and then the 3 selected classes will be randomized to the SIGMA condition, SSI-GP condition, and the active control condition by random numbers. All students in those classes will be invited to participate and the final participation depends on parental consent and students’ assent. Based on prior trials in local schools, about 60% of students are likely to agree to participate with parental consent. Thus, approximately 90 students will be recruited from each school.

After consenting, students will be asked to complete a battery of questionnaires (detailed below) via the Qualtrics survey system. The students in 1 class will be in the same intervention conditions. The interventions will be conducted separately for each group in the school activity rooms with sufficient computers or tablets and headphones. All intervention activities are self-administered and delivered in a web-based format. The principal investigator and well-trained research assistants will stay in the intervention rooms to provide guidance and help if needed. All groups in 1 school will be conducted concurrently or within 2 weeks to reduce the influence of the time factor.

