### Data Analysis

An intention-to-treat analysis will be conducted for any missing data. Two-level analyses will be used to account for cluster randomization [37]. To examine the effects of the interventions, multilevel regression will be used to test the group effect, time effect, and their interaction effect on outcome measures. Additionally, we will calculate effect sizes using estimated marginal means; these effect sizes compare mean gain scores (Cohen *d*), reflecting changes in each outcome from baseline to 2 follow-ups for youths receiving the mindset versus active control interventions. The effect sizes will also be compared between participants in the intervention group who receive booster messages and those who do not. A *P* value of <.05 will be considered statistically significant, and SPSS version 26 (IBM Corp) will be used for all statistical analyses.

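### Analysing only students who pass the attention checks at all three surveys contradicts the intention-to-treat plan, and a loosely defined duration rule eliminates further data after allocation

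*Protocol article*

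**What the plan says.** All references are to the protocol article.

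- **Attention rule** (Data Collection and Management): "Two attention-checking items will be included in the surveys of each time point for careless responding screening". The article then fixes the analysis set: "Only those who answer both attention-checking items correctly each time will be included in the final data analysis". Research Design gives three time points: baseline, 2 weeks and 8 weeks after the intervention.
- **Duration rule** (Implementation Strategies, fifth strategy): "Participants with too long and too short duration time (usually above 2 SDs) in 1 section will be double-checked on their participation effectiveness". The stated consequence is that "biased data will be eliminated".
- **Analysis principle** (Abstract, Methods): "We will use the intention-to-treat principle and linear regression-based maximum likelihood multilevel models for data analysis". Data Analysis adds: "An intention-to-treat analysis will be conducted for any missing data".
- **Order of events** (Participant Eligibility and Randomized Control Process): classes are randomised, then their students are invited, consent and complete the questionnaires.
- **Right to leave items blank** (Ethics Approval): students are told that they may skip any question.
- **Sample size** (Sample Size Determination): 146 per arm (438) are needed for d = 0.33 with 80% power. Recruitment is set at 183 per arm (549), because attrition in earlier school studies was below 20%.

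**The concern.** The attention rule selects persons, and it does so partly on what they do after the session. A student who is absent at 8 weeks, or who skips an attention item as the ethics text allows, cannot have answered both items correctly on every occasion. Read literally, the rule therefore drops nearly everyone with incomplete follow-up, along with students whose outcomes were observed but who failed a follow-up check. A likelihood-based multilevel model under intention-to-treat is meant to keep exactly these students. Nothing in the article labels the restricted set as per-protocol or as a sensitivity analysis.

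The duration rule also acts after allocation. Section times are recorded during the allocated session, and session content differs by arm: in Table 1 only SIGMA has an experiential exercise. What counts as biased data is not defined, the trigger is approximate, and the article does not say that the double-check is done without knowledge of arm.

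At stake is whether the primary comparison is between the classes as randomised or between the students who stayed attentive in each arm. There is also a loss of numbers for which the sample size makes no provision.

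**Working it through.** **1. The passages side by side.** The Abstract and Data Analysis promise intention-to-treat, the latter specifically for missing data. Data Collection and Management admits only students with correct answers on every occasion. Students with a missing survey are the ones the first statement is meant to handle and the ones the second excludes. Both cannot be followed as written.

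**2. Reproducing the plan's sample size.** With two-sided α = 0.05, power 0.80 and d = 0.33, n per arm = 2(1.960 + 0.842)² / 0.33² = 144.2, so 145. The exact t-test gives 145.1, so 146, as stated. Allowing for attrition, 146 / 0.8 = 182.5, so 183, and 3 × 183 = 549. Both figures reproduce.

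**3. Room left for exclusions.** 549 × 0.8 = 439.2 against 438 required. Per arm, 183 × 0.8 = 146.4 against 146. Since 1 − 146/183 = 0.202, attrition and exclusions together may not exceed about 20%.

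**4. Power if the attention rule is applied.** The failure rate f per survey is not in the article, so 5%, 10% and 15% are assumed, after 20% attrition. Two extremes are shown: failures independent across the three surveys, n = 146.4 × (1 − f)³, and the same students failing each time, n = 146.4 × (1 − f). Power = Φ(0.33 × √(n/2) − 1.96). No design effect is applied, as in the plan's own calculation.

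| f per survey | Independent: n per arm | Power | Same students: n per arm | Power |
|---|---|---|---|---|
| 0% | 146.4 | 0.81 | 146.4 | 0.81 |
| 5% | 125.5 | 0.74 | 139.1 | 0.79 |
| 10% | 106.7 | 0.67 | 131.8 | 0.76 |
| 15% | 89.9 | 0.60 | 124.4 | 0.74 |

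Recruitment that would restore 146 per arm is 146 / (0.8 × proportion kept): 213, 251 or 298 per arm with independent failures, and 193, 203 or 215 if the same students fail.

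**5. How many students a 2-SD trigger flags.** If section times were normal, 4.6% would lie outside 2 SD in one section. Over an assumed five independent sections, 1 − (1 − 0.0455)⁵ = 0.21. These students are flagged for checking; the article does not say what share would lose data.

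**6. Size of possible bias (illustration, all values assumed, no true effect).** If a fraction f of an arm is excluded and those students score s SD above the arm mean, the retained mean shifts by −s × f/(1 − f).

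- 25% against 15% excluded, s = 0.3: −0.100 + 0.053 = −0.047 SD.
- 25% against 15% excluded, s = 0.5: −0.167 + 0.088 = −0.078 SD.
- 20% in both arms, same s: 0.

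The first two are 0.047/0.33 = 14% and 0.078/0.33 = 24% of the planned effect, and they favour the arm with more exclusions.

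**The case against.** Screening out careless responses is legitimate, and several stronger readings go beyond the article.

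- **Every drop-out is certainly removed.** The rule might instead mean that only the failed survey is discarded, which would leave a role for the likelihood model. But the sentence describes which people are included, and the milder reading still throws away observed post-randomisation outcomes. The text needs changing on either reading.
- **Students with extreme times are deleted.** The article says that they "will be double-checked on their participation effectiveness, and biased data will be eliminated". It does not say that whole students, or their outcome scores, are removed. The Active Control Group section also says that the control has as many activities as the other arms and mirrors them closely. What stands is the undefined criterion and the silence on blinding; the blinded researcher in Data Collection and Management is mentioned for assessments only.
- **The focus criterion is a third post-randomisation exclusion.** A reader might infer this from "inability to stay focused to complete the intervention, which is approximately 45 minutes". It is listed as an eligibility criterion, the article does not say when it is judged, and all three sessions last 45 minutes. It does not support the point.
- **All three checks are equally harmful.** The baseline check follows class allocation but precedes the session, so session content cannot cause a failure.
- **Bias is established.** It is not. No passage links attention at follow-up to arm or to anxiety, and the bias is zero when exclusion rates and score shifts are equal.
- **Power must fall to 0.60.** That is the worst cell of an assumed range. Attrition is described as below 20%, so some slack may exist, and the article does not say whether that past figure already included data-quality losses.

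**Conclusion.** The point holds. The attention rule is a stated rule that conflicts with the stated analysis principle, not a detail left to another document, and it decides who enters the primary comparison. It should be corrected before analysis. The duration rule needs an objective definition and blinding to arm.

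The conflict rests on the wording alone and needs no assumption. The numbers do. With assumed failure rates of 5% to 15% per survey after the full 20% attrition, power at d = 0.33 is 0.60 to 0.79 before clustering, depending on how far the same students fail repeatedly. Bias is conditional: it arises only if exclusion, or its relation to anxiety, differs between arms. In the illustrated case it is about 0.05 to 0.08 SD. The article's sample size is arithmetically correct on its own inputs.

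**What to change.** - **Primary analysis set:** all consented students in randomised classes with at least one GAD-7 score, analysed as allocated, with all available surveys in the likelihood model. Because classes are randomised before students consent, this set is also formed after allocation, but it does not depend on follow-up attention or on time spent in the session.
- **Sensitivity analysis:** move exclusions for follow-up attention-check failure and for session duration here. Pre-specify an objective rule for each, including what counts as biased data, and apply it blind to arm.
- **Baseline check:** an exclusion for failing it may stay if it is applied before the session and identically in all arms. Its expected losses should then be added to the 20% allowance.
- **If the present rule is kept:** drop the intention-to-treat label and raise recruitment to cover the expected exclusions.

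The recommended change is one of wording. If no baseline exclusion is kept, recruitment stays at 549. The cost is that some careless responses remain in the primary analysis and add noise; the sensitivity analysis shows how much they matter.

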#### Content Fidelity Checking

##### Mindsets of Negative Emotions

The validated Chinese version 12-item Mindset of Depression, Anxiety and Stress Scale will be used to assess participants’ belief in change of negative emotion states, that is, depression, anxiety, and stress [16]. The sample items are “When you have a certain level of depression, you really cannot do much to change it”; “To be honest, people cannot really change how anxious they are”; and “No matter how hard people try, they cannot really change the level of stress that they have.”

Each item scores on a 6-point Likert scale; a higher score means a more fixed mindset of negative emotions (Cronbach α=.94). There are 3 subscales: depression mindset, anxiety mindset, and stress mindset, containing 4 items in each subscale. The Cronbach α of 3 subscales are .91, .89, and .90, respectively [16].

##### Mindset of Personality

Three items of implicit theory of personality [24,25] will be used to measure the belief in change of personality on a 6-point Likert scale from 1 (*strongly disagree*) to 6 (*strongly agree*). A higher score means a more fixed mindset. The sample item is “People can do things differently, but the important parts of who they are can’t really be changed.” The Cronbach αwas .85.

##### Intervention Feedback Scale

It is developed based on the theoretical framework of acceptability (TFA), which consists of 7 component constructs including affective attitude, burden, intervention coherence, perceived effectiveness, opportunity costs, self-efficacy, and ethicality [26]. Except for a general acceptability item, 6 items for the 6 components of TFA except for ethicality and 4 items including 2 open-ended written feedback items in regards to the impression of the intervention from the well-validated Program Feedback Scale [27] will also be integrated to assess the acceptability of the intervention. Among the final scale, except the open-ended item, the other 10 items will be assessed on a 5-point scale, such as “How acceptable was the intervention to you?” (“1=Completely unacceptable” to “5=Completely unacceptable”).

##### Motivation to Apply Things Learnt From the Program

Right after the intervention, we will ask participants after this program the extent to which they would like to apply the intervention content and the extent to which they would like to improve their emotion regulation on a 6-point Likert scale.

#### Primary Outcome

Anxiety symptoms measured by the Generalized Anxiety Disorder-7 (GAD-7) [28,29] are the primary outcome. The GAD-7 scale includes 7 items that assess whether anxiety symptoms have bothered the individual in the previous 2 weeks, ranging the frequency from 0 (*not at all*) to 3 (*nearly every day*). Example items were “Feeling nervous, anxious, or on edge” and “Not being able to stop or control worrying*.*” GAD-7 is the self-rating scale and effectively reflects symptom severity in adolescents; it is highly correlated with clinician-administered ratings of anxiety symptoms. It is brief and suitable for self-report study [30]. The Cronbach α was .93 [31].

#### Secondary Outcomes

##### Perceived Control

The Anxiety Control Questionnaire-Emotion Control [32] is a 15-item questionnaire that measures how much perceived control participants have over their anxiety. It is 1 of the 3 validated subscales of the anxiety control questionnaire and contains 4 items (eg, *I am able to control my level of anxiety*) rated from 0 to 5. The scale has a well-validated factor structure in a nonclinically selected sample, is strongly associated with anxiety and depression symptoms, and has demonstrated good internal consistency in previous investigations. The Cronbach α was .73.

##### Hopelessness

The 4-item helplessness subscale of the Demoralization Scale [33] will be used to measure the participants’ faith in the future. Each item scores on a 5-point Likert scale, and the mean of all 4 items is taken to measure the hopelessness, with a higher score meaning a correspondingly higher level of hopelessness. An example item is “I feel hopeless.” The Cronbach α of the Chinese version of this helplessness subscale was .72 [34].

##### Attitude Toward Seeking Help

We use 2 items from the Attitude toward Seeking Counselling Help Assessment [32,33], participants’ understanding of counseling and attitudes toward seeking counseling help. An example item is “If I believed I was having a mental breakdown, my first inclination would be to get professional attention*.*” The Cronbach α was .72 [34]. We develop a brief scale including 2 items to assess participants’ help-seeking behavior. The 2 items are “when I encounter difficulties, I will not ask help from teachers” and “when I encounter difficulties, I will not ask help from social workers/counsellors.” This scale will be rated on a 6-point Likert scale from 1 (very untrue of me) to 6 (*very true of me*).

##### Psychological Well-being

The short version Warwick-Edinburgh Mental Well-being Scale (WEMWBS-14) [35,36] will be used to measure the extent to which participants generally experience well-being states. The WEMWBS includes 14 items, scoring on 5-point Likert scale, the average of all 14 items indicates the well-being of the participants. The sample item is “I have been feeling optimistic about the future,” and the Cronbach α was .93.

#### Covariates

Sociodemographic information consists of a range of participant characteristics and is measured at the baseline to examine variability between the groups such as gender, age, grade, ethnicity, and socioeconomic status.

### Data Analysis

An intention-to-treat analysis will be conducted for any missing data. Two-level analyses will be used to account for cluster randomization [37]. To examine the effects of the interventions, multilevel regression will be used to test the group effect, time effect, and their interaction effect on outcome measures. Additionally, we will calculate effect sizes using estimated marginal means; these effect sizes compare mean gain scores (Cohen *d*), reflecting changes in each outcome from baseline to 2 follow-ups for youths receiving the mindset versus active control interventions. The effect sizes will also be compared between participants in the intervention group who receive booster messages and those who do not. A *P* value of <.05 will be considered statistically significant, and SPSS version 26 (IBM Corp) will be used for all statistical analyses.

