## Methods

### Research Design

This study will use a cluster-randomized control trial design. A conceptual model is provided in Figure 1. The intervention protocol will be pre-registered before data collection in ClinicalTrials.gov (ref: NCT05027880), and strictly follow the CONSORT (Consolidated Standards of Reporting Trials) guidelines [18,19]. At least 3 classes in the same grade of the participating school will be randomized (using computer-generated random numbers) into the (1) SIGMA group, (2) SSI-GP group, and (3) ST group (active control condition group), which will provide ST intervention at the same time. All participants will receive regular interventions in school. Three repeated assessments of the measures will be conducted for the 3 groups simultaneously at (1) baseline, (2) 2-week postintervention, and (3) 8-week postintervention (Figure 2). The cluster randomization at the classroom level can balance the risk of contamination between the intervention and active control groups and the school heterogeneity due to the school culture, schedule, and management.

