### Sample Size Determination

To make sure the sample size is big enough to test the hypotheses, a small to medium effect size (Cohen *d*=0.33) is used based on prior research [11], power set at 0.80, and α set at .05. A final sample size of 438 (146 per arm) is required. With reference to the attrition rate of our previous studies in a school setting, which is less than 20%, there is a requirement to recruit 549 participants at the baseline (183 per arm).

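### The planned difference-in-change contrast is valid but less efficient than adjusting for the baseline GAD-7 score already collected; prespecify baseline adjustment

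*Protocol article*

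**What the plan says.** The Research Design section lists the assessments as "1) baseline, (2) 2-week postintervention, and (3) 8-week postintervention", so baseline is one of three measurement occasions.

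The Data Analysis section calls for two-level analyses to reflect cluster randomization. Within them, "multilevel regression will be used to test the group effect, time effect, and their interaction effect on outcome measures". It continues: "Additionally, we will calculate effect sizes using estimated marginal means; these effect sizes compare mean gain scores", running from baseline to each of the two follow-ups and expressed as Cohen d. It does not name the SD that standardises d.

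The Covariates section lists only sociodemographic information, "measured at the baseline to examine variability between the groups such as gender, age, grade, ethnicity, and socioeconomic status". Baseline GAD-7 is not among the covariates, and no other section says the outcome model adjusts for it.

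Under Sample Size Determination, "a small to medium effect size (Cohen *d*=0.33) is used based on prior research", with "power set at 0.80, and α set at .05". No correlation between baseline and follow-up is given, and no intraclass correlation.

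**The concern.** The article fixes both the form of the test and the metric of the effect size, and both rest on change from baseline. If each arm has its own mean at baseline, as a model with a separate group effect normally allows, the group-by-time term at a follow-up is the between-arm difference in mean change. That is the same quantity as the gain-score comparison.

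Subtracting the baseline score in full over-corrects whenever the baseline to follow-up correlation is below 1. Two things follow:

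- **Precision.** The contrast has a larger variance than one that lets the data set the weight on baseline.
- **Chance imbalance.** An arm that happens to start higher tends to show a larger fall through regression to the mean, and the gain score keeps part of that fall. Classes are randomized, with about 6 per arm as a minimum (6 schools, at least 3 classes each), so some imbalance between arms is to be expected.

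The protocol itself anticipates a small effect (Discussion, Overview), so avoidable noise in the main contrast matters. The baseline score that would reduce it is already being collected.

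**Working it through.** **The plan's own figure.** For two independent means with d = 0.33, two-sided alpha 0.05 and power 0.80: n = 2(1.960 + 0.842)² / 0.33² = 144.2, so 145 per arm. The t-based solution is 145.1, rounded up to 146, which matches "A final sample size of 438 (146 per arm) is required". Dividing by 0.80 for attrition gives 146 / 0.80 = 182.5, so 183 per arm and 549 in all. The calculation reproduces, and it makes no stated use of baseline.

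**Individual-level comparison.** Let r be the correlation between baseline and follow-up GAD-7 (assumed; not in the documents), with outcome variance 1 at both times.

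- Gain score: variance 2(1 − r).
- Baseline-adjusted: variance 1 − r².
- Share of precision lost by gain scores: 1 − (1 − r²) / [2(1 − r)] = (1 − r)/2.

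Power is for 146 per arm, taking d = 0.33 on the raw-score SD and ignoring clustering.

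| r | Gain variance | Adjusted variance | Precision lost | SE smaller with adjustment | Power, gain | Power, adjusted |
|---|---|---|---|---|---|---|
| 0.4 | 1.20 | 0.84 | 30% | 16% | 73.0% | 86.8% |
| 0.5 | 1.00 | 0.75 | 25% | 13% | 80.5% | 90.2% |
| 0.6 | 0.80 | 0.64 | 20% | 11% | 88.3% | 94.1% |
| 0.7 | 0.60 | 0.51 | 15% | 8% | 95.4% | 97.7% |

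Outside this range the loss is 35% at r = 0.3 and 10% at r = 0.8. Ignoring baseline altogether gives 80.5% power, so below r = 0.5 the gain score does worse than not using baseline at all.

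**Allowing for class randomization.** For class means, r is replaced by R = [m·ICC·c + (1 − ICC)·r] / [m·ICC + 1 − ICC], where m is students per class and c is the class-level correlation between baseline and follow-up. The loss is then (1 − R)/2. Class size m = 24 to 30 comes from 438/18 = 24.3 and from about 90 students per school over 3 classes. ICC 0.01 to 0.05 and c = 0.8 to 0.95 are assumptions.

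- Largest loss: m = 24, ICC 0.01, c = 0.8, r = 0.4. R = (0.192 + 0.396)/(0.24 + 0.99) = 0.478; loss 26%.
- Smallest loss: m = 30, ICC 0.05, c = 0.95, r = 0.7. R = (1.425 + 0.665)/(1.5 + 0.95) = 0.853; loss 7%.

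**Chance imbalance.** With 6 classes of 24 per arm, the standard error of the baseline difference between two arms is √{(2/144)[1 + 23·ICC]}, which is 0.13 SD at ICC 0.01 and 0.17 SD at ICC 0.05. Given an observed imbalance D, the gain-score contrast is displaced on average by (1 − r)·D. For D = 0.15 and r = 0.5 that is 0.075 SD, or 0.075/0.33 = 23% of the planned effect. Using R instead (m = 24, ICC 0.02, c = 0.8, r = 0.5: R = 0.874/1.46 = 0.599), it is 0.401 × 0.15 = 0.060 SD, or 18%.

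**The case against.** The strongest reply is that nothing in the plan is wrong. A multilevel model with group, time and interaction is standard. Under randomization the difference in change is unbiased, and it matches the hypothesis of a larger reduction in anxiety. Three classes of the same grade in each school are split across the three arms, so school and grade are balanced by design. Chance imbalance is already part of the sampling variance. All of this stands. A reader might infer from the imbalance argument that the planned test is biased, but it is not: the displacement shown above averages to zero over randomizations.

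A second objection is that the gain-score sentence concerns supplementary effect sizes, not the test. That is true of the sentence alone. The sentence on the test nevertheless leads to the same estimand, since it includes a separate group effect and no baseline adjustment is named.

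A third is that the size rests on values the documents do not give. This also stands. A flat 15% to 30% cannot be stated as a fact about this trial: it needs r between 0.7 and 0.4 and a formula for individual randomization.

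The reply that such detail belongs in an analysis plan carries less weight, because the article does not leave the point open. It names the contrast and the effect-size metric.

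**Conclusion.** The point holds as a free improvement in efficiency and robustness, not as an error in the plan. It assumes that arm means are free at baseline, as the stated group effect implies. For assumed r = 0.4 to 0.7, the difference-in-change contrast gives up 30% to 15% of precision under individual randomization, and about 7% to 26% under the class-level assumptions above. In large samples, baseline adjustment is never less precise.

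Two stronger readings are tempting and are not supported:

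- **That this point shows the stated power is missed.** Ignoring clustering, the gain-score contrast keeps about 80% power or more at 146 per arm if r is at least 0.5 with d on the raw-score SD, and at any r if d = 0.33 is on the gain-score SD. Only the lower correlations with a raw-score d fall short (73% at r = 0.4). Any effect of clustering on power is a separate matter.
- **That the reported d will be on a different scale from the planned 0.33.** Neither Data Analysis nor Sample Size Determination names the standardiser, so a mismatch cannot be shown. The open choice does matter: at r = 0.6 the SD of gains is √0.8 = 0.894 of the raw SD, which alone would raise d by a factor of 1.12.

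**What to change.** Within the planned multilevel model, define the primary estimate as the arm difference in GAD-7 at 2 weeks and at 8 weeks, by one of two routes:

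- the 2-week and 8-week scores as outcomes, with baseline GAD-7 as a covariate; **or**
- all three occasions as outcomes, with the baseline mean constrained equal across arms (arm-by-follow-up terms, no arm effect at baseline).

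Name one route. They should not be mixed, because the second needs baseline as an outcome. Either still addresses the hypothesis of a larger reduction, since under randomization the arms share the same expected baseline.

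Treat the secondary outcomes in the same way. Compute Cohen d from the adjusted differences divided by the pooled baseline SD, and say so. If the expected benefit is described, show it as a range over assumed correlations.

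The cost is a few sentences of analysis wording. No further data, visits or participants are needed.
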